**Figure 1 figure1:**
[figure not shown]
Preliminary data showing differential tuberous sclerosis complex–associated neuropsychiatric disorders (TAND) severity trajectories in 21 participants over a period of 12 months. (A) The overall group maximum total TAND severity score (TTSS_max_) trajectories over the 12-month period with an average decline of 1% per month in TTSS_max_ over time. (B) Three different TAND severity trajectories with decreasing TTSS_max_ in 52% (11/21) of participants, increasing TTSS_max_ in 24% (5/21) of participants, and stable TTSS_max_ in 24% (5/21) of participants.

A range of individual factors have been identified that relate to TAND severity, including age, IA, genotype, and seizure characteristics, among others. While the impact of seizures and intellectual disability on TAND outcomes is widely accepted, neither seizures nor any of the other previously examined individual factors have been shown to be necessary or sufficient to cause any specific TAND manifestations or TAND clusters [5,25,33-35]. It is possible that the identification of differential TAND severity trajectories may help to clarify the role of these previously identified predictors; specifically, predictors may play different roles in different trajectory pathways. This is an important research question in TSC with direct relevance to clinical disease tracking and to inform pharmacological and nonpharmacological intervention studies of TAND.

### Caregiver Well-Being and TAND Severity

There is a growing evidence base for the psychosocial burden of TSC and TAND on individuals with TSC and their caregivers [9,36-39]. For this reason, the recent evidence-informed consensus recommendations for the identification and treatment of TAND [22] included a new “wraparound psychosocial cluster” in addition to the 7 natural TAND clusters previously identified [16-18]. However, the association between the psychosocial and other TAND clusters has received little attention in research to date. For this reason, the TAND-SQ included a question that contains 7 items on psychosocial difficulties experienced by the individual with TSC (question 8.1) and by their caregiver (question 8.2). Items enquire about low self-esteem, stress in the family, stress in relationships with siblings, parent-child relationship difficulties, parent-to-parent/partner relationship difficulties, stress leading to difficulty for the family to connect with others in their community, and career progress [20].

As part of the development of the TAND-SQ, data were collected through the TSC Alliance electronic self-report portal. This portal was added as a substudy to the existing TSC Alliance Natural History Database which allowed families or individuals to report on their own health outcomes [40,41]. TAND-SQ responses from 51 caregivers showed very high rates of psychosocial burden (Table 2). Notably, nearly 80% (40/51) of caregivers reported very high levels of stress in the family, and the majority reported very high parent-to-parent (26/51) and parent-child stress (28/51), as well as very high levels of stress making it difficult for the family to connect with others in the community (26/51).

**Table 2 table2:** Proportion of participants endorsing items related to caregiver psychosocial burden (question 8.2) on the self-report quantified tuberous sclerosis complex–associated neuropsychiatric disorders checklist (TAND-SQ; n=51).

TAND-SQ question 8.2 items	Values, n (%)
Low self-esteem	20 (39)
Very high family stress	40 (78)
Very high sibling stress	15 (29)
Very high parent-child stress	28 (55)
Very high parent-parent stress	26 (51)
Difficulty connecting in the community	26 (51)
Difficulty progressing in career	23 (45)

In the TSC community, caregiver burden has, to date, been conceptualized as a *consequence* of the severity of their family member’s physical TSC manifestations and TAND profile. Interventions have therefore been recommended to support improvement in TAND directly, both to reduce the severity of TAND and therefore caregiver burden. To a lesser extent, interventions to support caregivers and improve their coping skills have been recommended. However, there have been no investigations of the impact of caregiver well-being factors on the TAND severity of their family member with TSC, or to consider whether caregiver factors may mediate TAND severity outcomes (Figure 2A). A mediator is a variable that explains the impact of an independent variable (eg, intellectual disability) on a dependent variable (in this case, TAND severity). The implication of understanding caregiver well-being as a mediating factor is that interventions to support family caregivers’ well-being may have an impact not only on the caregiver directly but also indirectly on the TAND severity of their family members with TSC, thus making caregiver well-being factors “active ingredients” in the pathway toward closing the gap to treatment for TAND.

**Figure 2 figure2:**
[figure not shown]
Proposed tuberous sclerosis complex (TSC)–associated neuropsychiatric disorders (TAND) caregiver mediation model. (A) The proposed TAND caregiver mediation model. (B) Summary of the structural equation modeling results (n=51), where caregiver well-being was shown to mediate 40% of the relationship between intellectual disability and TAND severity. TAND-SQ: self-report quantified TAND checklist; TTSS_max_: maximum total TAND severity score.

In conditions outside rare genetic disorders such as TSC, findings are emerging about the fundamental role of caregivers and caregiver factors as mediators of the severity of their family members’ neuropsychiatric profile [42-44]. There have been no investigations of the impact of caregiver well-being factors on the TAND severity of their family members with TSC to consider whether caregiver factors may mediate TAND severity outcomes. A preliminary test of this hypothesis was conducted using data from the 51 participants from the TSC Alliance in the TANDem-1 project mentioned earlier. Structural equation modeling (SEM) was used to determine whether caregiver well-being mediated the relationship between the known TAND severity predictor of intellectual disability and overall TAND severity. Caregiver well-being was measured using the sum of items endorsed in question 8.2 of the TAND-SQ. IA was measured by question 5 of the TAND-SQ and coded as present or absent based on the caregiver’s view (question 5c), and overall TAND severity was quantified by the TTSS_max_. Findings are shown in Figure 2B and indicate that the presence of intellectual disability directly predicted both TAND severity (*c’*=47.93, SE 19.66; *P*=.01) and caregiver well-being (*a*=2.15, SE 0.65; *P*=.001). In addition, caregiver well-being was shown to mediate the impact of intellectual disability on TAND severity (*b*=15.02, SE 3.84; *P*<.001). Findings showed indirect effects of 32.33 (SE 12.78; *P*=.01) and a total effect of 80.26 (SE 20.35; *P*<.001), suggesting that caregiver well-being explained approximately 40% of the variance in TAND severity. This model acknowledges the potential role of individual factors (as independent variables), such as age, sex, genotype, age of seizure onset or control, in the pathway to TAND severity (Figure 2A, path *c’*), and accepts the need for direct and targeted interventions on TAND. However, the novelty of the hypothesis lies in the introduction of a mediation model via caregiver well-being (Figure 2A, path *a* and path *b*) to TAND severity and to different trajectories of severity. These findings provide the first preliminary support for a possible “TAND caregiver mediation model” and the need for further research in this area.

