**TSC characteristics (My TSC Story)**								
	Age diagnosed First concerns Current physical symptoms in each body system Genetic testing and genotype Seizure characteristics Treatments	My TSC Story		1-5		15 min		Individuals with TSC

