**Well-being**								
	Care/caregiving burden Brief Resilience Scale [82] Patient Health Questionnaire-9 [64] Generalized Anxiety Disorder 7-item scale [65] World Health Organization-5 Well-Being Index [83] Overall well-being rating	My Well-being		1-5		10 min		Individuals with TSC (only self-report); caregivers (only self-report)

^a^TAND-SQ: self-report quantified TAND checklist.

To support longitudinal data collection, the app includes built-in features to encourage retention. There will be automated “reminders” for new data collection time points through in-app notifications and emails to participants. Efforts have been made to ensure each data collection time point is not too time-consuming. Data collection for time point 1 will take approximately 60-70 minutes. At time points 2-5 (T_2_-T_5_), the total data collection time should be faster as several items within the My TSC Story, My TAND Checklist, and My TAND Interventions sections will be prepopulated, thus only requiring updates to be completed. We anticipate data collection at time points T_2_-T_5_ to take 30-40 minutes. We will include visual summaries of the data entered by participants, which will allow them to view changes in their TAND severity over time. These are intended to encourage participants to return to the app for data entry at the subsequent time points. The app will generate PDF summaries of information provided by participants that can be downloaded and shared with health care teams. The app contains the TAND toolkit, developed as part of the TANDem-1 project [20], containing a range of evidence-informed suggestions for what additional clinical help to seek and what can be tried at home for symptoms across all TAND clusters. Access to the TAND toolkit is also considered a retention strategy.

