#### Statistical Analysis Plan (Aim 2)

The caregiver dataset will be analyzed as follows: first, SEM will be used for mediation modeling of baseline data (T_1_). Next, trajectory classes and their predictors identified in aim 1 will be combined with mediators confirmed through SEM to analyze the mediated association between predictors and latent trajectory classes using a generalized structural modeling approach. Separate mediation models will be fit for different combinations of individual risk factors, caregiver well-being measures, and TAND severity outcomes. Additionally, we will extend the structural equation model to incorporate multiple individual factors and multiple caregiver well-being measures for specific TAND severity outcomes, including sequential mediation models that use successive measurements of caregiver well-being as the successive mediators [87]. All analyses will be done using R [85,88].

Using our preliminary analyses regarding a possible “caregiver mediation model” with intellectual disability (binary variable) and TTSS_max_ (274 in the TANDem-1 sample; Figure 2), mediated through caregiver stress (maximum of 7 units), assuming effect size for path *a*=2.15 (SE 0.65) and path *b*=15.02 (SE 3.84), 100 observations will have 95% power to detect a mediation effect=40% of the total effect at the 5% level of significance according to Sobel test for mediation [89]. If we decrease the effect sizes for *a* and *b* by 50%, 300 observations will have 86% power to detect a significant mediation effect.

We will control for false discovery rates due to multiple comparisons as a result of potentially multiple models for the multiple outcome-mediator-predictor combinations using the Benjamin Hochberg procedure [90]. The inclusion of relevant covariates in the models will be identified through directed acyclic graphs [91].

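### In the Aim 2 baseline mediation model one caregiver reports both mediator and TAND outcome, so shared-rater error can yield a significant path b with no caregiver effect

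*Protocol article*

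**What the plan says.** The Introduction (Caregiver Well-Being and TAND Severity) describes the preliminary model. The respondents are caregivers: "TAND-SQ responses from 51 caregivers showed very high rates of psychosocial burden". All three variables come from their TAND-SQ form:

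- Exposure: intellectual disability, "coded as present or absent based on the caregiver’s view (question 5c").
- Mediator: "Caregiver well-being was measured using the sum of items endorsed in question 8.2 of the TAND-SQ".
- Outcome: "overall TAND severity was quantified by the TTSS_max".

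In the main study, Table 3 places question 8.2 inside the same TAND-SQ that describes the person with TSC. The well-being scales (resilience, PHQ-9, GAD-7, WHO-5, burden) are listed as "Individuals with TSC (only self-report); caregivers (only self-report"). Table 3 names no second informant, clinician rating or objective TAND outcome.

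Statistical Analysis Plan (Aim 2) starts with a structural equation model on the baseline data of the caregiver dataset. Mediators confirmed there are carried into the models for trajectory classes. It also states: "Separate mediation models will be fit for different combinations of individual risk factors, caregiver well-being measures, and TAND severity outcomes". The stated safeguards are covariates chosen from directed acyclic graphs and the Benjamini-Hochberg procedure. The Introduction and Short-Term Impact read a positive result causally, with caregiver factors acting on TAND severity.

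**The concern.** Path b is the mediator-outcome association given the exposure. It equals a caregiver effect only if the errors in mediator and outcome are uncorrelated given the covariates. When one person fills in both scales, mood or response style can move both, and the residuals then correlate without any effect on TAND itself.

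Aim 2 is meant to show whether caregiver well-being is a target for improving TAND. A change in TAND and a change in how TAND is rated look the same in a cross-sectional single-informant model. A mediator accepted on that model alone may be a rating effect, and it then feeds the later trajectory models.

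**Working it through.** **Inputs from the Introduction (n=51).** Path a: "caregiver well-being (*a*=2.15, SE 0.65; *P*=.001"). Path b = 15.02 (SE 3.84). Total effect = 80.26.

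**The plan's own figures reproduce.**
- Indirect effect: 2.15 × 15.02 = 32.29 (stated 32.33).
- Sobel SE: √(2.15² × 3.84² + 15.02² × 0.65²) = √(68.16 + 95.32) = 12.79 (stated 12.78).
- Mediated share: 32.33 / 80.26 = 40.3%.
- Power at n=100: z = (32.29 / 12.79) × √(100/51) = 3.54, and Φ(3.54 − 1.96) = 94% (stated 95%).
- Power at n=300 with both paths halved: z = 3.06, power 86.5% (stated 86%).

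These calculations treat all of path b as a caregiver effect.

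**Strength of the preliminary path b.** t = 15.02 / 3.84 = 3.91. As a partial correlation this is 3.91 / √(3.91² + 48) = 0.49 (0.48 from the residual SDs below).

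**Residual SDs, assuming 50% prevalence of intellectual disability.**
- Mediator: 0.65 × √(51 × 0.25) = 2.32.
- Outcome given mediator: 3.84 × 2.32 × √51 = 63.6.
- Outcome given exposure only: √(63.6² + (15.02 × 2.32)²) = 72.6.

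**False path b when true b = 0.** For error correlation ρ, the expected b is ρ × 72.6 / 2.32 and the false mediated share is 2.15 × b / 80.26.

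| ρ (assumed) | False b | False share | Sobel significant, n=300 | Sobel significant, n=430 |
|---|---|---|---|---|
| 0 | 0 | 0% | about 5% | about 5% |
| 0.1 | 3.1 | 8% | about 40% | about 53% |
| 0.2 | 6.3 | 17% | about 93% | about 99% |
| 0.3 | 9.4 | 25% | 100% | 100% |

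The rejection rates come from simulation with least-squares paths, a two-sided 5% Sobel test and path a = 2.15. The n=430 column assumes that about 86% of 500 participants are caregivers, as in the 21 repeat completions (18/21). Prevalences of 0.3 and 0.7 left the ρ = 0.2 result at n=300 at 93%. At ρ = 0.05 the rate is only 14% at n=300 and 18% at n=500. With path a halved and ρ = 0.2 it is 83% at n=300.

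**Role of path a.** A false b needs only shared error in mediator and outcome. A false indirect effect also needs a non-zero path a. The preliminary data report one, and the Introduction describes burden as a consequence of TSC and TAND, so the condition is met on the protocol's own terms.

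**Do the stated safeguards help?** Benjamini-Hochberg controls chance findings, not a systematic bias. Graph-based covariates help only if the rater component is measured. Response style is not, and mood (PHQ-9, GAD-7) is itself a candidate mediator.

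**Does the longitudinal data help?** This was simulated with a stable rater factor, true b = 0 and an assumed wave-to-wave TAND correlation of 0.8 to 0.9. At ρ = 0.2 a lagged path b without adjustment stays significant in about 93–99% of studies. Adding baseline TAND cuts this to about 12–29%, and at ρ = 0.1 to about 7–12%. Rater mood that varies over time is not removed by this adjustment; no size was estimated for it.

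**The case against.** Five points on the other side deserve weight.

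1. No passage gives a size for shared-rater error, or shows that distressed caregivers rate higher. This stands. The correlations are assumptions, and small ones do little.
2. The Introduction reports that the severity scores relate to clinical diagnoses and standardized behavioural measures. This supports the scale's validity but does not exclude a rater component.
3. Aim 2 goes on to trajectory classes. A constant response style shifts level more than slope, although classes may also differ in baseline level. This stands: the figures above cover the baseline model only.
4. The false share at ρ of 0.1 to 0.2 (8–17%) is well below the reported 40%. True, but Aim 2 confirms mediators by significance, and that is where the error enters.
5. Sensitivity analyses are often left to a full analysis plan, and Potential Challenges and Solutions admits that the preliminary data are limited. Their absence alone would be no finding. What the article does fix is confirmation through the baseline model and a causal reading of it; the limitation it admits is sample size, not the single informant.

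A reader might infer that a significant path b must be false, or that the preliminary 40% is an artefact. The documents do not support either. A ρ near 0.48 to 0.49 would reproduce the 40%, but nothing shows that ρ is that large. A reader might also infer that lagged models are useless because the same rater supplies every wave. That is wrong for a stable response style once earlier TAND is adjusted for.

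**Conclusion.** The concern holds for the baseline structural equation model of Aim 2, as a possibility that the plan does not control. With no caregiver effect on TAND, an assumed mediator-outcome error correlation of 0.1 gives a significant Sobel test in about 40% (n=300) to 53% (n=430) of studies, and 0.2 in about 93% to 99%. This rests on path a at its preliminary value, a linear model, and correlations that the documents do not supply. It does not show that Aim 2 will reach a false conclusion, and it does not quantify the bias in the trajectory-class models. A mediator confirmed on the baseline model alone cannot be told apart from a rating effect, so the causal reading does not follow from that step.

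**What to change.** In Statistical Analysis Plan (Aim 2):

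1. For every mediator called confirmed at baseline, report the mediator-outcome error correlation at which the indirect effect becomes zero, and the one at which its confidence interval includes zero. Set no pass/fail cut-off unless the sponsor prespecifies one; the documents give no basis for a particular value.
2. Do not confirm a mediator on the baseline cross-sectional model alone. Also report path b from a lagged model adjusted for baseline TAND severity, using waves already planned. State that rater mood varying over time can still bias it.
3. Unless the result survives these checks, word the Aim 2 conclusion as an association with caregiver-rated TAND severity.

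It is tempting to use a caregiver-reported physical outcome as a comparison, such as the Table 3 item "Current physical symptoms in each body system". It would not serve: the Introduction treats physical manifestations as a cause of caregiver burden, so a link there could be real and not a rating effect.

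The cost is analysis wording and a few extra model runs, with no new data. Some mediators may no longer count as confirmed.

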### Strengthening Caregiver Well-Being

There is a global emphasis on policies and programs that support caregiver skills to promote the development of their children and family members with developmental disabilities [45,46]. However, to date, very little attention has been paid to the capacity of caregivers to care [47]. With a limited capacity to care, it is difficult for caregivers to incorporate or implement new knowledge, skills, or techniques, often worsening a caregiver’s sense of competence [48,49].

In the context of these findings and given the highlighted burden of caring for an individual with TSC [9,36,37] (and possible mediation effect of caregiver well-being and TAND severity), we propose a creative solution to improve caregiver capacity to care. Acceptance and commitment therapy (ACT, pronounced as “act”) is an established process-based cognitive behavioral therapy designed to promote psychological flexibility [50]. Psychological flexibility has been defined as “one’s ability to fully attend to the present time, think with openness, and work to advance one’s life in personally meaningful ways” [51]. Tools such as metaphors and experiential exercises are used to help individuals learn how to make healthy contact with difficult thoughts, feelings, memories, and physical sensations that they may have feared or avoided in the past. Participants learn how to make a nonjudgmental space for these painful thoughts, feelings, and memories while developing greater clarity about their personal values and committing to small changes in behavior in line with these values [50]. A growing body of evidence suggests that ACT interventions can result in positive changes in psychological flexibility and, in turn, in the psychosocial well-being of caregivers of children with a range of psychological and physical difficulties, including autism, chronic pain, and significant health needs [52-57]. The findings of these studies and reviews support ACT as a transdiagnostic intervention and suggest that even very brief interventions can have psychosocial benefits for caregivers [58,59]. In TSC, no studies to date have examined the potential feasibility of ACT to support caregiver well-being.

The World Health Organization (WHO) drafted a prepublication stand-alone Caregiver Well-being module as part of the WHO Caregiver Skills Training Program for caregivers of children with developmental delays, disabilities, or disorders [60,61]. The module consists of three 2-hour sessions where 2 trained facilitators meet once a week with a group of about 10 caregivers. Facilitators use a manualized facilitator guide to deliver the intervention. In partnership with the WHO, researchers in South Africa used a participatory approach to perform the first adaptation and evaluation of the Caregiver Well-being module with South African families with children who had a range of developmental disabilities. The work resulted in the novel “Well-Beans for Caregivers” intervention, which was delivered in a low-resourced rural community in one of the South African provinces to 10 caregivers, including 1 with a child who had TSC [62]. A specialist facilitator led the intervention, cofacilitated by a nonspecialist (the mother of a child with autism and employee of the national autism nonprofit organization in South Africa). Caregivers had a mean age of 41.27 (SD 11.07) years, almost all of them were single parents, and had no tertiary education. Their children were an average of 8 (SD 2.36; range 4-11) years of age, with diagnoses including autism, intellectual disability, ADHD, epilepsy, and TSC. Almost half had developmental delays in motor milestones, recapitulating a profile very similar to that seen in TSC. Feasibility was evaluated with attendance tracking, completion rates of digital data collection forms, feasibility evaluation of group sessions, and competence of the specialist facilitator (rated by nonspecialist facilitators and observers). Acceptability was evaluated through acceptability ratings of group sessions by caregivers, facilitators, and observers. Potential efficacy was evaluated using 6 standardized and validated measurement tools, including the Acceptance and Action Questionnaire II, a measure of psychological flexibility [63], the Patient Health Questionnaire-9 (PHQ-9), a measure of parental depression [64], the Generalized Anxiety Disorder 7-item scale (GAD-7) [65], the Multidimensional Scale of Perceived Social Support (MSPSS), a measure of caregiver perception of community support [66], the Family Impact of Childhood Disability Scale (FICDS), a measure of positive and negative appraisal of disability [67], and the Brief Measure of Parental Well-being [68].

Results showed very high attendance rates for each of the 3 sessions (session 1: 9/10, 90%; session 2: 10/10, 100%; session 3: 9/10, 90%), and form completion was 100%. The feasibility of group sessions was rated as very high for facilitator competency (mean 92.67, SD 6.43) and training of others (mean 93.33, SD 4.5). Acceptability of the groups was rated as high by the caregivers, facilitators, and observers. Despite the small sample size, pre-post efficacy measures showed medium to large effect sizes (r, where r=Z/N is the nonparametric effect size) on 7 of the 10 measures, and large effect sizes (r>0.5) on 5 measures, including the PHQ-9 (r=0.52), GAD-7 (r=0.56), MSPSS Total (r=0.58), and FICDS (positive impact, r=0.64). These preliminary data showed strong early-phase evidence to proceed to the next step in the clinical trials pipeline [62].

In summary, there is a clear need in the TSC field to build on the findings of the TANDem-1 project and current TAND literature by exploring longitudinal trajectories of TAND severity and what personal factors and TSC characteristics may predict these trajectories. This is important to inform clinical care and make prognostications about TAND severity. Research is also needed to better understand caregiver well-being in TSC and how it may act as a mediator of TAND severity and TAND severity trajectories. Elucidating these relationships is important for identifying targets of treatment for TAND severity. Finally, it is of utmost importance to learn more about how to support caregivers in their chronic caregiving journey. These needs are the basis for the aims of the TANDem-2 project.

The TANDem-2 project will be carried out by the TAND consortium, originally formed in the TANDem-1 project and expanded for TANDem-2 to consist of 33 adult members (>18 years of age) from 16 different countries around the world, with 11 members being family representatives (individuals with TSC or family members of individuals with TSC). Other consortium members include TSC professional stakeholders, technology developers, global TSC stakeholders, and established and emerging TAND researchers. Here we present the aims, objectives, measures, data collection procedures, data analysis methods, data protection, data management, and ethical considerations for the TANDem-2 project.

